## Abstract

**Background:**

Understanding the cost and/or cost-effectiveness of implementation strategies is crucial for organizations to make informed decisions about the resources needed to implement and sustain evidence-based interventions (EBIs). This economic evaluation protocol describes the methods and processes that will be used to assess costs and cost-effectiveness across implementation strategies used to improve the reach, adoption, implementation, and organizational maintenance of an evidence-based pediatric weight management intervention- Building Health Families (BHF).

**Methods:**

A within-trial cost and cost-effectiveness analysis (CEA) will be completed as part of a hybrid type III effectiveness-implementation trial (HEI) designed to examine the impact of an action Learning Collaborative (LC) strategy consisting of network weaving, consultee-centered training, goal-setting and feedback, and sustainability action planning to improve the adoption, implementation, organizational maintenance, and program reach of BHF in micropolitan and surrounding rural communities in the USA, over a 12-month period. We discuss key features of implementation strategy components and the associated cost collection and outcome measures and present brief examples on what will be included in the CEA for each discrete implementation strategy and how the results will be interpreted. The cost data will be collected by identifying implementation activities associated with each strategy and using a digital-based time tracking tool to capture the time associated with each activity. Costs will be assessed relative to the BHF program implementation and the multicomponent implementation strategy, included within and external to a LC designed to improve reach, effectiveness, adoption, implementation, and maintenance (RE-AIM) of BHF. The CEA results will be reported by RE-AIM outcomes, using the average cost-effectiveness ratio or incremental cost-effectiveness ratio. All the CEAs will be performed from the community perspective.

**Discussion:**

The proposed costing approach and economic evaluation framework for dissemination and implementation strategies and EBI implementation will contribute to the evolving but still scant literature on economic evaluation of implementation and strategies used and facilitate the comparative economic analysis.

**Trial registration:**

ClinicalTrials.gov NCT04719442. Registered on January 22, 2021.

**Supplementary Information:**

The online version contains supplementary material available at 10.1186/s43058-022-00287-1.

Contributions to the literature
We report a novel framework to assess costs and cost-effectiveness across implementation strategies used to improve the RE-AIM outcomes of an evidence-based pediatric weight management interventionWe identify and present the strategy costs across RE-AIM dimensions to clarify sometimes fuzzy boundaries between these strategiesWe provide a pragmatic and replicable methodology for costing dissemination and implementation (D&I) strategies to help stakeholders or community organizations decide what strategies are most efficient at achieving the goal of adoption, implementation, and sustainability and demonstrate the usability of the proposed time-tracking tool to facilitate cost assessments of D&I strategies in the community settings

## Background

Childhood obesity is associated with increased risk for a variety of cardiovascular and other diseases and has been documented to predict adult obesity which results in personal health challenges and imposes an economic burden to the healthcare system [1, 2]. Although pediatric weight management interventions (PWMIs) or prevention programs are becoming prevalent, families from micropolitan (i.e., cities <50,000 populations) and surrounding rural areas have limited access to PWMIs that are typically offered in larger urban areas. Expanding the availability of evidence-based PWMIs and increasing capacity in micropolitan regions to implement these interventions can have a significant public health impact. Systems-based approaches that engage multiple community-organizational partners to share implementation responsibility have been proposed as a potential pathway to increasing PWMI access in micropolitan communities [3].

Integrated system-based approaches typically include horizontal components (i.e., engagement of organizations across a community) and vertical components (i.e., engagement of administrative decision makers and staff that would ultimately implement the PWMI) [4]. Both horizontal and vertical system components provide opportunities for applying dissemination and implementation (D&I) strategies that may improve the likelihood that evidence-based PWMIs can be adapted, adopted, implemented, and sustained in micropolitan areas [3, 5]. For example, a fund and contract strategy, involving research funding announcement, application review, and contractual agreements for implementation, can be used to improve the adoption of PWMIs in communities with the readiness for implementation [6]. Moreover, the use of an action learning collaborative (LC) strategy that encompasses a variety of activities to support communities in improving PWMI reach, effectiveness, adoption, implementation, and maintenance (RE-AIM [7]) (e.g., structured learning/training sessions, goal-setting and feedback, sustainability action planning) can be used to increase community engagement across organizations and facilitate capacity building for PWMI implementation [8, 9].

Despite the proposed promise of these approaches, it is necessary to understand both the ability of these strategies to improve RE-AIM outcomes as well as the costs and resources needed to execute D&I strategies [10–12]. Unfortunately, study findings from those that have conducted economic evaluations of D&I strategies are mixed and thus the economic feasibility of D&I strategy use remain unclear. In studies that have applied economic analysis of LCs [13, 14], a cost-effectiveness analysis (CEA) focusing on pre-post changes in clinician’s competency on trauma-focused cognitive behavioral therapy and youth’s trauma-related mental health found the LC did not produce a favorable cost-effectiveness ratio with clinician competency as the outcomes measure. However, the subsequent reductions in youth psychopathology demonstrated a high cost-effectiveness. More broadly, two recent review studies [15, 16] identified articles examining the costs, consequences, and cost-effectiveness of strategies designed to influence the adoption of public or population-level interventions in community settings. Both reviews shared the methodology limitation that the number of studies that they identified and synthesized, especially among studies associated with the implementation or implementation strategies, and a plethora of terms and definitions of D&I strategies making cross-study comparisons related to CEA challenging. Moreover, no detailed discussion of costing methods was found in their reviews.

As a result of the challenge of summarizing CEAs relative to D&I strategies, there is a movement to increase the specification of both D&I strategies and the resulting economic evaluation [17]. The recent effort made by the “Economics and Cost” action group of the Consortium for Cancer Implementation Science is an example of this movement. In a series of papers [10–12, 18], this effort provided common definitions, costing methods, developing costing guidance, and guidance to build collaborations across disciplines [19]. Complementary to the collection of articles, this paper provides a description of an economic evaluation across various D&I outcomes using RE-AIM [7] and methods to cost D&I strategies mapped to specific outcomes related to PWMI implementation in micropolitan settings. Specifically, it outlines the methods and processes of the prospective within-trial economic evaluation of D&I strategies to be undertaken within a hybrid type III effectiveness-implementation (HEI) trial to improve RE-AIM outcomes of evidence-based PWMIs in micropolitan communities. We will examine costs and cost-effectiveness of D&I strategies focused on enhancing PWMI (1) reach (i.e., the number, proportion, and representativeness of program participants relative to the intended audience), (2) adoption (i.e., the number and proportion of communities that agree to deliver the PWMI), (3) implementation (i.e., adherence to program protocol), (4) organizational maintenance (i.e., sustained implementation to addition cohorts of families over time), and (5) their overall impact on the effectiveness (i.e., reduction in BMI z scores). The cost-effectiveness results will provide data for payers, policymakers, and providers to make informed decisions about specific strategies for specific RE-AIM outcome targets, especially in organizations or communities where resources are scarce.

## Methods

### Study design

This economic evaluation protocol is embedded within a type III HEI trial, aiming to test multilevel D&I strategies that focus on the RE-AIM outcomes of an evidence-based PWMI (i.e., Building Health Families [BHF] [20–22]). Details of the overarching trial have been published elsewhere [3, 5, 23] and information on that trial is presented here as it relates to the economic evaluation of strategies that target RE-AIM outcomes (see Table 1). Specifically, the trial includes three primary D&I strategies—fund and contract, an online, packaged implementation blueprint, and an action LC. In addition, the implementation blueprint includes activities focused on training, program implementation, and referral resources to improve program reach. Similarly, the LC includes activities focused on network weaving, used to promote information sharing within and outside the organizations building upon existing working relationships [6], consultee-centered training, and sustainability action planning. The study is intended to (1) identify local demand for BHF, a PWMI that was used as the basis for the online, packaged implementation blueprint (referred to hereafter as the BHF Online Training Resources and Program Package [5]); (2) examine potential determinants of BHF adoption; and (3) compare BHF RE-AIM outcomes in communities that participate in the LC to those that do not. As a pilot type III HEI, the primary aim is to determine if the LC communities document better D&I outcomes (reach, adoption, implementation, BHF sustainability) and the secondary aim is to determine the relative effectiveness of BHF between communities that participate in the LC versus those that do not. Of note, regardless of LC participation status, communities are exposed to strategies of fund and contract and BHF Online Training Resources and Program Package. The trial protocol is registered with clinicaltrials.gov (NCT04719442).

**Table 1 Tab1:** Cost and outcome measures for the within-trial economic evaluation by the RE-AIM outcomes

Outcomes	Corresponding strategy	Cost of BHF-LC (C_**LC**_)	Cost of BHF-PO (C_**PO**_)	Outcome measure (E)	ACER/ICER	Interpretation
**R**each	-LC- consultee-centered training focusing on recruitment at schools and clinics -Develop a packaged implementation blueprint- referral process	-LC training and consultation sessions -BHF recruitment training -Recruitment activities	-BHF recruitment training -Recruitment activities	-Number, proportion, & representativeness of eligible families screened	C_LC_-C_PO_/E_LC_-E_PO_	Cost of per additional person recruited
**E**ffectiveness	-BHF program training and delivery	-All LC activities -BHF program training and delivery	-BHF program training and delivery	-Reduction in BMI *z*-scores	C_LC_-C_PO_/E_LC_-E_PO_	Cost per additional BMI *z*-score reduced
**A**doption	-Fund and contract	-Response to RFA from potential community stakeholders and organizations	-Response to RFA from potential community stakeholders and organizations	-Objective count of communities responding to RFA and contracted to implement BHF	C_all_/E_all_	Cost per community adoption
	-LC- consultee-centered training with focus on BHF cohort adoption -Develop a packaged implementation blueprint- BHF online training resources & package	-LC training and consultation sessions -Online training and program packaging -BHF program training and delivery	-Online training and program packaging -BHF program training and delivery	-Objective count of # of BHF cohorts initiated	C_LC_-C_PO_/E_LC_-E_PO_	Cost per additional cohort initiated
**I**mplementation	-LC- consultee-centered training with focus on implementation fidelity	-LC training and consultation sessions	None	-Average fidelity scores from the direct observation	C_LC_/E_LC_-E_PO_	Cost per additional changes in fidelity scores
	-Develop a packaged implementation blueprint- BHF online training resources & package	-Online training and program packaging	-Online training and program packaging	-Average knowledge check scores from BHF online training resources -Summarized implementation fidelity assessed via direct observation.	C_all_/E_all_	Cost per knowledge score/unit of implementation fidelity
**M**aintenance- setting level	-LC- sustainability action planning	-LC training and consultation sessions	None	-Objective count of BHF cohort continued	C_LC_/E_LC_-E_PO_	Cost per additional 3rd cohort initiated

*RE-AIM* Reach, effectiveness, adoption, implementation, and maintenance, *BHF* Building Healthy Families, *LC* Learning collaborative, *PO* Package only, *RFA* Request for application, *ACER* Average cost-effectiveness ratio, *ICER* Incremental cost-effectiveness ratio, *LOI* Letter of intent

Each of the D&I strategies is described below. To ensure clear communication and transparency, we used Proctor and colleagues’ framework [24] to specify implementation strategies. The specification of each D&I strategy by the *actor* (who enacts the strategy?), the *action*(s) (what are the specific actions, steps, or processes that need to be enacted?), the *action target* (what constructs are targeted? What is the unit of analysis?), *temporality* (when is the strategy used?), *dose* (what is the intensity?), and implementation *outcome* (what implementation outcome(s) are likely to be affected by each strategy?) is presented in Table 2. We also individually assess the costs of each strategy.

**Table 2 Tab2:** Labor activity specification of dissemination and implementation strategies used in the HEI trial by the Proctor framework [24]

Strategy [3]	Outcome^**a**^	Action	Actor	Action target	Temporality	Dose (frequency)	Dose (duration)^**c**^
**Develop packaged implementation blueprint**^**b**^ • BHF Online Training Resources and Program Package • Referral process	**Reach** -Number, proportion, & representativeness of eligible family screened	-Training activities on developing referral channels across media, school, and clinical sources.	-Electronic resource and research team	BHF-LC & BHF-PO	Early	One module that can be repeated	As needed
	**Adoption** -Objective count of the number of BHF cohorts initiated	-Training material modification -Program resource provision	-Electronic resource and Research team -Trifoia	BHF-LC & BHF-PO	Early	18 training modules	Duration of each programming & trouble shoot
	**Implementation** -Observed adherence to protocol and increased facilitator capacity	-Monitor training progress and the completion of knowledge & fidelity checklists	-Project coordinator	BHF-LC & BHF-PO	Early-mid	18 training modules	Duration of each training session
**Fund and contract** • Network weaving (recruitment of community) • Obtain formal commitment	**Adoption** -Objective count of communities & organizations responding to call for letter of intent -Objective count of communities & organizations responding RFA and contracted to implement BHF	-Draft the LOI -Draft the full application -Review the application materials -Meetings to discuss the applications & make a decision -Contact with the awardees -Obtaining the written memorandums	-Research team & CAB -Research team & CAB -Research team -Research team & CAB -Project coordinator -Project coordinator	Interested communities	Early	One-time for interested community	Duration of the meetings/telecommunications
**Learning Collaborative**^**b**^ • Network weaving (recruitment of BHF participants) • Consultee-centered training • Sustainability action planning	**Reach** -Number, proportion, & representativeness of eligible family screened -Representativeness of participating low-income families	-Document screening & engagement of low-income families -Create learning session materials that focus on identifying recruitment sources and channels to improve reach—with an emphasis on schools and clinics. -Delivery learning sessions that provide opportunities for community implementation teams to action plan recruitment procedures -Provide individual/group consultation on recruitment methods and outcomes -Follow up on action plans and outcomes using lighting report protocol -Provide action period consultation and reporting opportunities	-Research team -Research team -Research team -Research team -Research team -Research team	BHF-LC	Early-mid	Frequency of the sessions focusing on reach	Duration of the sessions
	**Adoption** -Objective count of the number of BHF cohorts initiated	-Create learning session materials -Delivery learning sessions -Provide individual/group consultation -Conduct knowledge/fidelity checklist -Provide feedback at each learning session -Complete pragmatic evaluations	-Research team -Research team -Research team -Research team -Research team -Research team	BHF-LC	Mid-late	Frequency of the training sessions focusing on adoption	Duration of the sessions
	**Implementation** -Observed adherence to protocol and family engagement at each BHF session -Instructor self-reported fidelity at each BHF session	-Create learning session materials -Delivery learning sessions -Provide individual/group consultation -Conduct knowledge/fidelity checklist -Provide feedback at each learning session -Complete pragmatic evaluations	-Research team -Research team -Research team -Research team -Research team -Research team	BHF-LC	Mid-late	Frequency of the training sessions focusing on implementation	Duration of the sessions
	**Maintenance** -Survey/checklist at 12 months -Objective count of sustained implementation of cohorts in the year following completion of the LC intervention	-Develop sustainability needs assessment checklists -Develop funding matrix development tools -Develop key partner identification and engagement -Develop an ongoing assessment & feedback -Conduct sustainability needs assessment -Examine current and future resources, payer and payment models -Integrate into regular learning meetings & action periods	-Research team & CAB -Research team -Research team -Research team & CAB -Research team -Research team & CAB -Research team	BHF-LC	Late	Frequency of activities/events focusing on maintenance	Duration of the activities

*BHF* Building Healthy Families, *LC* learning collaborative, *PO* Package only, *CAB* community advisory board, *LOI* Letter of intent

^a^Costs are divided among RE-AIM (reach, effectiveness, adoption, implementation, and maintenance) outcomes and are estimated with actions/activities specified for that specific outcome

^b^Costs are divided among implementation outcomes associated with the strategy, based on the activities specified in the action column

^c^Preparation time and travel time (if any) and post-session follow-up (e.g., summary note) are also included

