### Eligibility, recruitment, and allocation

#### Community level

Applying the community engagement approach, the research team and the BHF-CAB disseminated the RFA within and outside their organizations and networks (i.e., applying network weaving strategy) and documented that communities across all 93 counties received the RFA. Eight communities with broad geographic distribution responded to the RFA of which seven rural communities in Nebraska completed a full proposal and were selected as the participating communities for the HEI trial. We then ranked the seven applications in a descending order and allocated the odd-numbered rankings to the (BHF-LC) and the even-numbered rankings to the package-only (BHF-PO) condition [23]. This exercise resulted in four communities in the BHF-LC condition and three communities in the BHF-PO condition. All communities that implement the PWMI will have access to the BHF Online Training Resources and Program Package that includes all of the materials necessary to implement and evaluate the BHF intervention.

Communities assigned to the BHF-PO condition are required to complete a memorandum of agreement (i.e., obtaining formal commitment strategy) to report on the implementation of the PWMI and to use pragmatic evaluation strategies for reach and effectiveness outcomes and to provide de-identified program data for baseline, 6, and 12 months. These communities will also have technical support as needed related to package function, but no other facilitation. Communities allocated to the BHF-LC condition will participate in LC training lessons with additional embedded implementation support activities with a goal to (1) develop local strategies to screen and engage families through the BMI Reporter in schools or clinical screening and referral, (2) increase implementation fidelity, and (3) plan for sustainability.

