### Effect measurement

The outcomes measured across implementation strategies and BHF intervention are described in Table 1. At the community level, the outcome associated with the fund and contract dissemination strategy is BHF program adoption, defined as (1) an objective count of communities responding to call for LOI and full application and (2) an objective count of communities responding to RFA and contracted to implement BHF. In addition, the BHF Online Training Resources and Program Package strategy targets outcomes of adoption, measured as an objective count of numbers of BHF cohorts initiated, and implementation, operationalized as community facilitator competence using the knowledge check score obtained from the BHF online training resource and direct observation of implementation fidelity (i.e., adherence to protocol, engagement, and dose [i.e., the number and duration of sessions conducted per cohort]). Finally, the LC implementation strategy involves outcomes of (1) reach, measured as the number, proportion, and representativeness of eligible family screened; (2) adoption, measured as an objective count of BHF cohorts initiated; (3) implementation fidelity, measured using the fidelity checklist via direct observation conducted by the trained research staff; and (4) sustainability, operationalized as an objective count of BHF cohort continued following the completion of LC sessions.

At the individual level, the effectiveness outcome will be assessed using a matched cohort design to determine changes in BMI *z*-scores from baseline to 6 and 12 months among BHF intervention participants across BHF-LC and BHF-PO conditions. We will apply an intention-to-treat approach when conducting the economic evaluation of the BHF intervention (effectiveness as the outcome measure).

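### The reach ICER divides by eligible families screened but is labelled as cost per person recruited, so it cannot be read as a cost per recruit

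*Protocol article*

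**What the plan says.** All places are in the Protocol article.

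- **Table 1, reach row (Study design).** The outcome E is "Number, proportion, & representativeness of eligible families screened". The ratio is printed as "C_LC_-C_PO_/E_LC_-E_PO", meaning incremental cost over incremental effect. The interpretation column reads "Cost of per additional person recruited".
- **Table 2 (Study design).** For both the packaged blueprint and the LC, the reach outcome is "Number, proportion, & representativeness of eligible family screened". The LC entry adds "Representativeness of participating low-income families".
- **Effect measurement.** The LC outcome is "reach, measured as the number, proportion, and representativeness of eligible family screened".
- **Background.** Reach is defined differently: "reach (i.e., the number, proportion, and representativeness of program participants relative to the intended audience".
- **Data analysis.** An ICER is the extra cost for one extra unit of the outcome measured. ICERs will be compared with thresholds drawn from previous economic research.
- **Community level.** One goal of the LC is to "develop local strategies to screen and engage families through the BMI Reporter in schools or clinical screening and referral".

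**The concern.** The row's numerator, strategy and interpretation all concern recruitment, but its denominator counts screening. The article treats these as separate events: it speaks of screening and of engaging families, and Table 2 lists participating families apart from screened ones. Nothing in the article converts screened families into recruited persons.

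If the plan is followed as written, a figure in dollars per screened family will be published under a label that says dollars per recruited person. A payer or community would take it as the price of bringing one more participant into the programme, and any comparison with an external threshold would use the wrong unit. The LC can also move the denominator directly, because screening through schools and clinics is one of its stated goals. A favourable reach ICER therefore need not mean that more families took part.

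**Working it through.** The article gives no reach cost, screening count, conversion rate or numerical reach ICER, so there is no stated figure to reproduce. The check is algebraic, with labelled illustrations.

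**Inputs from the article**
- Denominator as specified: eligible families screened, S (Table 1, Table 2, Effect measurement).
- Denominator as labelled: persons recruited (Table 1).
- Persons per family, k: 12 families are put at 30–48 individuals (Individual level), so k = 30/12 = 2.5 to 48/12 = 4.
- Each cohort holds 5 to 12 families; the goal is 2 cohorts per community (Individual level).
- Communities: 4 in BHF-LC and 3 in BHF-PO (Community level).

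**Formulas.** Let F be families recruited and Δ the LC-minus-PO difference.
- As specified: ICER_S = ΔC/ΔS
- Per family recruited: ICER_F = ΔC/ΔF, so ICER_F/ICER_S = ΔS/ΔF
- Per person recruited: ICER_P = ΔC/(kΔF), so ICER_P/ICER_S = ΔS/(kΔF)

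If the same fraction c of screened families enrols in both arms, then ΔF = cΔS and the factors are 1/c and 1/(kc).

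| c (assumed) | per family, 1/c | per person, k = 2.5 | per person, k = 4 |
|---|---|---|---|
| 0.1 | 10.0 | 4.0 | 2.5 |
| 0.2 | 5.0 | 2.0 | 1.25 |
| 0.4 | 2.5 | 1.0 | 0.625 |
| 0.5 | 2.0 | 0.8 | 0.5 |
| 0.8 | 1.25 | 0.5 | 0.31 |
| 1.0 | 1.0 | 0.4 | 0.25 |

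A factor above 1 means the printed ratio understates the labelled quantity; below 1, it overstates it. Per person, the switch comes at c = 1/k, that is 0.40 for k = 2.5 and 0.25 for k = 4.

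**Illustrations** (assumed ΔC = $10,000; all counts and conversions assumed)

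1. *Equal conversion.* Screened 60 against 40, c = 0.4 in both arms. ΔS = 20; ΔF = 24 − 16 = 8. ICER_S = $500 and ICER_F = $1,250. The printed figure is too low for families by a factor of 2.5.
2. *More screening, same enrolment.* Screened 100 against 40, with 24 families enrolled in each arm. ΔS = 60; ΔF = 0. ICER_S = $167, while the cost per additional recruit is undefined.
3. *LC raises conversion.* Screened 45 against 40, c = 0.5 against 0.25. ΔS = 5; ΔF = 22.5 − 10 = 12.5. ICER_S = $2,000 and ICER_F = $800. The printed figure is now too high.

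Where recruits are a subset of those screened, ΔF exceeds ΔS only if fewer families are screened without enrolling under the LC than under PO. In illustration 3 these are 45 − 22.5 = 22.5 and 40 − 10 = 30.

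**The case against.** The best defence is that the screening denominator is deliberate: Table 1, Table 2 and Effect measurement all use it, and only the interpretation cell and the Background differ. On that view the fault is one mislabelled cell. The trial's primary aim, whether LC communities achieve better reach, does not depend on how an economic ratio is labelled. Participation is not ignored either, since Table 2 tracks the representativeness of participating low-income families. All of this stands. It supports relabelling as the minimum correction, but it does not make the present label right.

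Three stronger readings are tempting, and the article does not support them.

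- *The label will always make recruitment look too cheap, by some 2 to 10 times.* That range assumes equal conversion of 0.5 to 0.1, and the article gives no conversion rate. The direction also reverses if the LC lifts conversion, which is plausible because it aims to engage families and consults on recruitment methods. Counting individuals at 2.5 to 4 per family pushes the same way.
- *Enrolment per community can only be 10 to 24 families* (2 × 5 to 2 × 12). Two cohorts is a goal. Cohorts initiated, including a third cohort, are outcomes in Table 1. Only the limits per cohort are stated.
- *The ratio rewards indiscriminate mass screening.* Only eligible families count, so screening ineligible children earns no credit. What remains is narrower: screening more eligible families without extra enrolment improves the ratio.

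**Conclusion.** The point holds as a mismatch of event and unit that is visible within one table row and conflicts with the Background definition of reach. Under the Data analysis rule, the planned ratio is a cost per additional eligible family screened and cannot be reported as a cost per recruit.

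For families, it probably understates the cost per additional recruit. That rests on recruits being a subset of the eligible families screened and on the LC not raising conversion enough to make ΔF exceed ΔS. The size, ΔS/ΔF, cannot be fixed from the article. For individuals, the direction is open. The mismatch itself is certain; its numerical effect is not. It should be corrected before results are reported, because it decides what the reach ratio can be said to show.

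**What to change.** 1. Label the existing Table 1 ratio *cost per additional eligible family screened*.
2. Add a reach ICER with families enrolled as the single scalar E, labelled *cost per additional family enrolled*. It may instead replace the screening ratio as the reach ICER, in line with the Background definition. Report proportion and representativeness descriptively: E now lists three quantities, and representativeness cannot serve as a denominator.
3. Put costs and effects on a per-community basis, because the arms have 4 and 3 communities.
4. Report the screened-to-enrolled yield by condition, so that readers can see how the two ratios relate.
5. Make the reach wording agree in the Background, Table 1, both reach entries of Table 2, and Effect measurement.

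The cost is mainly wording and one further ratio. Screening counts are already needed. Package-only communities already agree to report on reach and supply de-identified programme data, and participant check-in sheets are planned. One drawback is that the enrolment ICER may be unstable, or undefined, if enrolment differs little between arms. Incremental cost and incremental enrolment should therefore be shown beside it.
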